#### 2.4.2 Demographics, Anthropometric and Clinical Data

Demographic information will be collected at baseline, including age, sex, nationality, occupation, marital status, residence and education level. Anthropometric measures mainly include body mass index (BMI), waist and hip circumference, heart rate and blood pressure. Clinical data including blood lipids, blood biochemical findings, immune and inflammation markers and imaging examinations will be gathered from baseline and specified visit points.

#### 2.4.3 Data Collection

After the screening, all qualified participants with LADA will enter a 1-month washout period. After the stable control of diabetes with insulin, all enrolled participants will complete the baseline survey for a period of 1 week. The primary endpoint results will be collected after 3 months of intervention. Then, participants will receive outpatient visits every 3 months until the end of the study. The research assistants involved in data collection and evaluation will not be informed of the grouping of participants. The evaluation and data collection process is shown in **Table 1**. The participants will record their daily dose of medications, abnormal self-monitoring of blood glucose levels, combined medications and adverse events. Before each visit, participants will be asked to fill out an online survey of nutritional status in the past week to assess calorie intake, including the content of carbohydrates, fat, protein and fiber in the diet. Nurses will instruct patients to record the type and quantity of daily food *via* online and mobile platforms. In addition, it is worth noting that participants should not consume fermented dairy products (such as yogurt) or probiotics 7 days before the visit and should avoid high-fat diets 3 days before the visit.

**Table 1 T1:** Patient flow of enrolment, intervention and outcome measurements.

		PS	M0	M3	M6	M9	M12
**Enrolment**	Recruitment	×					
	Eligibility Screening	×					
	Informed consent	×					
	Allocation		×				
**Intervention**	Insulin injection	•					•
	Experimental drugs / placebo		•	•			
**Outcomes**	Demographic characteristics (Age, sex, nationality, occupation, marital status, residence and education level)		×				
	Anthropometric variables (BMI, waist and hip circumference, heart rate and blood pressure)	•					•
	Insulin logs		•				•
	Dietary logs		•				•
	CGMS*		•				•
	Metabolic parameters (HbA1C, FBG, PBG, FCP, 2hCP, Triglyceride, Total cholesterol, HDL cholesterol, LDL cholesterol)	•					•
	HOMA-IR**		•				•
	Insulin autoantibody (GADA, IA2A, ZnT8)	×	×	×			×
	Serum inflammation markers		×	×			
	Chronic complication screening (Carotid ultrasound, UCG, fundus examination, urinary albumin-creatinine ratio, eGFR)		×				×
	Gut microbiota (Metagenomics, stool metabolomics, plasma metabolomics)		×	×			×
	Intestinal permeability		×	×			×
	Drug safety assessment (Blood routine, Liver and kidney function testing, Serum electrolytes, Blood ketones, electrocardiogram)		×	×			
	Quality of Life Questionnaire***		×	×			×
	Adverse events record (hypoglycemic events and drug-related side effects)		×	×			

PS, prior to study; M0, baseline assessment; M3, 3 months from the baseline; M6, 6 months from the baseline; M9, 9 months from the baseline; M12, 12 months from the baseline. *CGMS, continuous glucose monitoring system; **HOMA-IR, homoeostasis model assessment index for assessing insulin resistance; ***questionnaire: CN-ADDQoL.

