**Methods and Analysis:**

We will conduct a single-center, prospective, randomized, double-blind, placebo-controlled trial. A total of 240 patients with LADA who have started insulin therapy will be randomly allocated either to the intervention or control group. After a 1-week run-in period, they will complete a 3-month treatment of BBR alone, inulin plus BBR, inulin alone, or placebo. Anthropometric and clinical data will be collected at five time points: baseline, 3 months, 6 months, 9 months, and 12 months from baseline. The primary outcome was the change in glycated hemoglobin levels. Dynamic blood glucose parameters, β-cell function, and gut microbiota, as well as adverse events and quality of life will be monitored.

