## 2 Methods

### 2.1 Trial Design

This is a prospective, randomized, double-blinded, placebo-controlled trial with a 1-month washout period, a 1-week run-in period, a 3-month treatment period, and a 9-month follow-up period. The participants will be arranged to enter a 1-month washout period after obtaining their informed consent during which basic treatment medications are adjusted, and then they will be allocated to enter a 1-week run-in period for lifestyle education and collection of baseline data and samples. After the run-in period, they will be randomized 1:1:1:1 to one of four groups: BBR-alone, inulin plus BBR, inulin-alone, or placebo. This study will use a stratified random method to balance the following factors: BMI ≥25 kg/m^2^ and <25 kg/m^2^, with or without chronic complications of diabetes. Measurements will be implemented at baseline prior to the intervention and at 3 months, 6 months, 9 months and 12 months from baseline. The research flowchart is shown in **Figure 1**.

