### 2.3 Interventions

All participants who sign the informed consent will first enter a 1-month washout period during which insulin is used as basal therapy to avoid interference of previous hypoglycemic therapy on the study results. The proportion of patients treated with insulin will be comparable in each group. According to the individual characteristics of each subject, the investigator and the physician in charge should determine the brand, dosage form, initial injection dose and frequency of insulin. The optimal glycemic control target is fasting blood glucose (FBG) in the morning <7.2 mmol/L and 2 hours postprandial blood glucose (PBG)<10.0 mmol/L. The dose and dosage form of insulin will be adjusted or switched based on the subjects’ average blood glucose level over the three days preceding each visit. Other antidiabetic drugs will be prohibited throughout the study. After completing the screening and evaluation, the research nurses will implant the dynamic blood glucose monitor subcutaneously for the participants and advise them on the appropriate nursing measures. Prior to the intervention, participants will receive a 1-week diabetes health education as well as a baseline assessment. Then, they will be randomly divided into the following four groups: BBR (0.6 g per 6 pills, twice daily before meals) plus inulin (0.6 g per 6 pills, twice daily before meals), BBR plus placebo (inulin), inulin plus placebo (BBR), or placebo (inulin) plus placebo (BBR). BBR is manufactured by Yabang Epson Pharmaceutical Co., Ltd., Yancheng, Jiangsu, China. Inulin was purchased from Sino Peptide Health Technology Co., Ltd., Beijing, China, and its raw material supplier was Cosucra in Belgium. If desired, inulin can be processed into different dosage forms. The placebos are similar in appearance to BBR and inulin. Each type of tablet is packaged uniformly in an opaque sealed bottle with instructions and labels. The care providers and participants will be blinded to the assignment of medicine. After 3 months of treatment, participants will be asked to return the drug packages to determine their compliance. Researchers will conduct regular follow-up by telephone with all the participants to encourage and improve medication compliance, and record related adverse events including hypoglycemia and gastrointestinal symptoms.

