### 2.5 Data Analysis

Data analysis will be performed using SPSS 26.0 software (IBM, New York, USA). P<0.05 was regarded as statistically significant unless otherwise specified. Descriptive statistics included the mean ± standard deviation for normal distributions, median and interquartile range for otherwise, and frequency and percentage for categorical variables. Intention-to-treat analysis (ITT) will be used and multiple imputations will be handled to manage missing data. Baseline descriptive data between the control group and the intervention groups will be compared using the chi-square test for categorical variables, and ANOVA for continuous variables. The primary outcome of HbA1c will be expressed as the mean HbA1c values with standard deviations, and ANOVA will be used to compare HbA1c between groups. According to the data distribution characteristics, ANOVA or Wilcoxon rank sum test will be used to compare the changes in secondary variables within and between groups. If the difference is significant, pairwise comparisons will be performed with adjustment for multiple comparisons, and ANCOVA will be used with confounding factors such as sex and age as covariates. Spearman’s correlation analysis and partial Spearman’s correlation analysis adjusted for sex and age will be used to evaluate the relationship between changes in intestinal microbial abundance and other markers.

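### The primary HbA1c test in section 2.5 is an unadjusted ANOVA; an unconditional ANCOVA on baseline HbA1c and the stratification factors would be more precise at no cost

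*Protocol article*

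**What the plan says.** - **Outcome.** Section 2.4.1 makes the primary outcome the change in mean HbA1c, measured at baseline and 3 months.
- **Primary test.** Section 2.5 reports HbA1c as means with standard deviations and states that "ANOVA will be used to compare HbA1c between groups". It does not say whether M3 values or changes are compared.
- **Covariates.** ANCOVA appears later in 2.5, conditional on a significant difference, with sex and age as examples. Baseline HbA1c is not named. Neither are the section 2.1 stratification factors (BMI below or at least 25 kg/m², chronic complications present or absent).
- **Within-group comparisons.** Section 2.5 plans these for secondary variables only.
- **Timing of baseline.** Section 2.1 describes a trial "with a 1-month washout period, a 1-week run-in period, a 3-month treatment period, and a 9-month follow-up period", with the "1-week run-in period for lifestyle education and collection of baseline data and samples" coming after the washout. Section 2.4.3 adds: "After the stable control of diabetes with insulin, all enrolled participants will complete the baseline survey for a period of 1 week". No HbA1c criterion for stability is given.
- **Insulin.** Section 2.3 describes a "1-month washout period during which insulin is used as basal therapy to avoid interference of previous hypoglycemic therapy on the study results" for everyone who consents, and lets insulin be adjusted or switched around each visit. The same section wants the share of insulin-treated patients to be similar across groups. The abstract says: "A total of 240 patients with LADA who have started insulin therapy will be randomly allocated either to the intervention or control group".
- **Screening value.** In Table 1 the metabolic parameters, HbA1c among them, run from the pre-study column (PS) to M12.

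**The concern.** HbA1c reflects glycaemia over a period longer than the five weeks between the start of the washout and M0. A patient whose treatment changed at the start of the washout may therefore still have a moving HbA1c at M0, and titration continues afterwards. Patients also arrive with different treatment histories, so the movement may differ between them. That adds spread to the M3 values, and a model without baseline HbA1c leaves this spread in the error term.

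Two things are at stake. One is the precision of the primary comparison, which is planned at only 80% power. The other is interpretation: an HbA1c fall within one arm, placebo included, could come from insulin and say nothing about berberine or inulin. An ANCOVA run only after a significant ANOVA helps with neither, because the primary test has already been made without it.

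**Working it through.** **1. The plan's sample size.** Inputs from section 2.1.2: difference 0.44, SD 0.80, two-sided α 0.05, 80% power. The normal approximation gives n = 2(1.96 + 0.8416)² × 0.80² / 0.44² ≈ 51.9, so 52 per arm. The exact t calculation gives 79.3% power at 52 and 80.1% at 53. The stated 53 is reproduced. Going from 53 to 60 allows for 7/60 = 11.7% attrition.

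**2. Interval before baseline.** 1 month + 1 week ≈ 5 weeks from the start of the washout.

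**3. Possible shared movement after M0.** Drift = −(1 − f) × F, where F is the total HbA1c fall from the change in insulin treatment and f is the share already expressed at M0. Both are assumptions.

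| F | f = 0.5 | f = 0.65 | f = 0.8 |
|---|---|---|---|
| 0.5 | −0.25 | −0.17 | −0.10 |
| 1.0 | −0.50 | −0.35 | −0.20 |
| 1.5 | −0.75 | −0.52 | −0.30 |

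For patients already settled on insulin, F may be near zero.

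**4. Does this bias the comparison?** Two arms of 53 were simulated, 3,000 runs per setting, with F = 1.0 (patient-to-patient SD 0.5) and f from 0.5 to 1.0.
- With no drug effect, both arms fall by 0.50, 0.35, 0.20 or 0.00 at f = 0.5, 0.65, 0.8 or 1.0. The between-arm estimate stays at 0.00, with type I error about 4–5% for ANOVA of M3 values, ANOVA of changes, ANCOVA on M0, and ANCOVA on M0 plus screening.
- With a true effect of 0.44, all four return about −0.44.

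**5. Precision from M0 HbA1c.** Take SD 0.80 at both visits, n = 53 per arm, and correlation ρ between M0 and M3 (assumed). The residual SD is 0.80√(1 − ρ²) for ANCOVA. The SD of the change is 0.80√(2 − 2ρ).

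| ρ | ANOVA of M3 | ANOVA of change (SD) | ANCOVA on M0 (SD) |
|---|---|---|---|
| 0.4 | 80% | 73% (0.876) | 86% (0.733) |
| 0.5 | 80% | 80% (0.800) | 90% (0.693) |
| 0.6 | 80% | 88% (0.716) | 94% (0.640) |

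Against M3 values the gain is 6, 10 or 14 points. Against change scores it is about 14, 10 or 6, so it is the smaller of the two only when ρ exceeds 0.5. In the simulation, where M0 and M3 are strongly related, power was 74–75% for M3 values, 93–98% for change and 94–98% for ANCOVA. There a change-score analysis already captures nearly all of the gain.

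**6. Adding screening HbA1c.** Let ρ₀ be the M0–M3 correlation, ρₛ the screening–M3 correlation and ρ₀ₛ the screening–M0 correlation, all assumed. Power with M0 alone, then with both:
- (0.5, 0.4, 0.7): 90.0% to 90.1%
- (0.6, 0.6, 0.7): 93.9% to 95.9%
- (0.6, 0.2, 0.8): 93.9% to 99.1%, the most favourable setting tried

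Most settings give 0 to 2 points. In the simulation the four ranges overlap and screening adds next to nothing.

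**The case against.** The strongest reply is that nothing here threatens validity. The trial is randomised, double-blind and placebo-controlled, and shared movement cancels between arms; step 4 bears this out. That stands. It also means that setting a common drift of 0.10 to 0.75 beside the 0.44 design effect compares unlike things, because 0.44 is used as a difference from placebo.

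A reader might infer that the plan treats a within-arm HbA1c fall as efficacy. It does not: section 2.5 confines within-group comparisons to secondary variables and compares HbA1c between groups.

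A reader might also infer that all patients switch to insulin at the washout, so that every baseline is unstable. The documents do not settle this. The abstract describes patients already on insulin, and section 2.3 speaks both of insulin for all during the washout and of a proportion treated with it.

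Finally, a condensed article may leave the covariate list to an analysis plan, and sex and age are only examples. That is fair as to the exact list. It does not cover what the article does state: ANOVA for the primary outcome, and ANCOVA conditional on significance. That choice is fixed, and a better one is available.

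**Conclusion.** The point holds as one of precision and clarity, not of bias. Section 2.5 leaves unused two sources of precision the trial already has: baseline HbA1c and the stratification factors. It makes covariate adjustment depend on the result it should have informed. It also leaves unclear whether the ANOVA is on M3 values or on the change that section 2.4.1 names.

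For correlations of 0.4 to 0.6, adjusting for M0 is worth 6 to 14 power points over ANOVA of M3 values. If changes are already being analysed, the benefit shrinks as the correlation rises above 0.5. The correlations are assumptions, and the power figures are for one pairwise comparison with placebo, as in the plan's own calculation.

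Movement of HbA1c after M0 is plausible, but the documents give no figure for it. It is no ground for calling the sample size wrong or for changing the washout. Screening HbA1c is an optional extra.

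**What to change.** In section 2.5:

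1. Make the primary analysis an ANCOVA of M3 HbA1c on arm, M0 HbA1c and the two stratification factors (BMI group, chronic complications), run whatever the result of any other test. Screening HbA1c may be added as a prespecified covariate, with little gain expected.
2. State that any within-arm HbA1c change is descriptive and is not evidence of a drug effect.

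Separately, reconcile the abstract and section 2.3 on which patients are on insulin at entry and from the washout onwards.

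The cost is a few sentences. The covariates are already collected, and no extra visit, sample or patient is needed.

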#### 2.1.1 Participants

The target population of the trial will be LADA patients between the ages of 30 and 70. Participants will be recruited at a large tertiary first-class hospital in Hunan, China. The following inclusion criteria will be used in the recruitment:

Participants of both sexes aged 30 to 70 with a BMI between 18.5 and 37.5 kg/m^2^; with diabetes diagnosed according to the diagnostic criteria of the World Health Organization (WHO) in 1999; positive glutamic acid decarboxylase antibody (GADA) and HbA1c level ≥ 7.0% and ≤ 10.0%; being insulin-independent for more than 6 months after diagnosis; diabetes duration less than 5 years; fasting serum C-peptide (FCP) level ≥0.15 nmol/L, or 2-hour postprandial C-peptide (2hCP) level ≥0.3 nmol/L; and providing written informed consent will be included.

Participants will be excluded from the trial if they (1) have severe liver dysfunction (ALT and AST levels greater than three times the upper limit of detection); (2) have an eGFR < 50 ml/min/1.73 m^2^; (3) have evidence of acute or chronic infection affecting glycemic control within 4 weeks prior to the first visit; (4) have a history of any malignancy; (5) are pregnant/breastfeeding women; (6) have secondary diabetes; (7) have acute complications (ketoacidosis, lactic acidosis or hyperosmolar coma); (8) have severe organic heart disease, including but not limited to congenital heart disease, rheumatic heart disease, hypertrophic or dilated cardiomyopathy, etc., New York Heart Association (NYHA) heart function classification ≥Grade III; (9) have used corticosteroids or immunosuppressants for over 3 months, or other medications that can cause gastrointestinal reactions 2 months before recruitment and throughout the whole study period; (10) have a history of hemolytic anemia or glucose-6-phosphate dehydrogenase deficiency; and (11) are allergic to berberine hydrochloride or any components in the combinations.

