### 2.4 Outcome Assessment

#### 2.4.1 Primary and Secondary Outcomes

The primary outcome measure is the change in mean HbA1c level, measured at baseline and 3 months post-intervention, which reflects the blood glucose management status of the participants.

The secondary outcome measures include: (1) the frequency of hypoglycemic events and drug-related side effects; (2) the change in C-peptide for assessing β-cell function and the incidence of acute and chronic diabetes complications; (3) daily insulin dose and medical service utilization, such as diabetes-related hospital admissions and emergency visit rate; (4) the alteration of gut microbiota assessed by multiomics measurements and the differences in intestinal permeability; and (5) the quality of life assessed by the Audit of Diabetes Dependent Quality of Life (ADDQoL-19) containing physical functioning, symptoms, psychological well-being, social well-being, role activities and personal constructs with its Chinese version CN-ADDQoL also having the individualized properties, satisfactory reliability and validity (Cronbach’s alpha=0.941) (26).

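### The microbiota–marker correlations adjust for sex and age only, so treatment arm (and, to a lesser degree, intercurrent infection with antibiotics) can produce associations that do not exist within arms

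*Protocol article*

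**What the plan says.** Gut microbiota is part of the fourth group of secondary outcomes in section 2.4.1: "the alteration of gut microbiota assessed by multiomics measurements and the differences in intestinal permeability". Table 1 places the sampling at M0, M3 and M12.

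For the link between microbiota and metabolism, section 2.5 plans plain and partial Spearman correlations to "evaluate the relationship between changes in intestinal microbial abundance and other markers". It names sex and age as the covariates of the partial version. The threshold is general: "P<0.05 was regarded as statistically significant unless otherwise specified". The article does not say whether the four arms are pooled.

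Four provisions bear on outside influences on the samples:
- a dietary rule before visits (section 2.4.3): "participants should not consume fermented dairy products (such as yogurt) or probiotics 7 days before the visit", together with a three-day restriction on high-fat diets;
- an entry exclusion for patients who "have evidence of acute or chronic infection affecting glycemic control within 4 weeks prior to the first visit" (section 2.1.1, item 3);
- a medication exclusion (section 2.1.1, item 9), which covers corticosteroids and immunosuppressants "or other medications that can cause gastrointestinal reactions 2 months before recruitment and throughout the whole study period";
- a participant log (section 2.4.3): "The participants will record their daily dose of medications, abnormal self-monitoring of blood glucose levels, combined medications and adverse events".

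Antibiotics are not named anywhere in the article, and no analytic use of the medication log is stated.

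**The concern.** Randomisation makes arms comparable. It does not make patients with a large microbial change comparable with patients with a small one. A correlation between two changes that both occur after randomisation is observational, and anything that moves both will create it.

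The clearest common cause is the treatment itself. The Abstract describes berberine as antidiabetic and antibacterial, and inulin as altering the gut microbiota and improving glycaemic control. If the drugs work as hoped, arm shifts both variables. In pooled data a taxon that berberine suppresses will then correlate with HbA1c change, even if the taxon has nothing to do with glycaemia. Sex and age are balanced across arms by design, so adjusting for them removes none of this.

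A second common cause is an infection during the study that is treated with antibiotics. It can disturb the microbiota and also raise glucose or inflammation markers.

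What is at stake is the reading of these correlations as a link between microbial and metabolic change, not the trial's main result.

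**Working it through.** **1. The plan's own figure.** Section 2.1.2 gives a difference of 0.44%, SD 0.80%, two-sided α 0.05, power 80% and 53 evaluable patients per arm. The normal approximation is n = 2 × (1.960 + 0.842)² × (0.80/0.44)² = 51.9, so 52. The t-test solution is 52.87, so 53, with power 80.1%. The figure reproduces. Evaluable total: 4 × 53 = 212.

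**2. Inputs for the arm effect.**
- Marker shift: 0.44/0.80 = 0.55 SD, from section 2.1.2, applied to the two berberine arms (half of the patients).
- Taxon shift in the same arms: 0.3 to 1.0 SD. This is an assumption; the article gives no figure.
- Within-arm association: none.
- Arms pooled: an assumption.

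**3. Size of the induced correlation.** With half of the patients shifted by d₁ (taxon) and d₂ (marker), the covariance is 0.25·d₁·d₂ and each variance is 1 + 0.25·d². So

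ρ = 0.25·d₁·d₂ / √[(1 + 0.25·d₁²)(1 + 0.25·d₂²)].

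- d₁ = 0.3: 0.04125 / √(1.0225 × 1.0756) = 0.039.
- d₁ = 1.0: 0.1375 / √(1.25 × 1.0756) = 0.119.

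The standard error of a null correlation is about 1/√211 = 0.069. An expected ρ of 0.119 lies 0.119/0.069 = 1.73 standard errors from zero, and the chance of exceeding 1.96 is then about 41%.

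**4. Simulation.** 4,000 replicates, n = 212, test at P<0.05. Sex and age were generated independently of both changes. Share of significant results:

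| Taxon shift (SD) | Spearman | Partial: sex, age | Partial: sex, age, arm |
|---|---|---|---|
| 0 | 5.2% | 5.1% | 4.8% |
| 0.3 | 8.4% | 8.3% | 4.7% |
| 0.5 | 15.5% | 15.4% | 5.2% |
| 0.8 | 28.8% | 28.8% | 5.2% |
| 1.0 | 40.9% | 40.3% | 4.6% |

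The planned adjustment changes almost nothing. Adding arm returns the rate to about 5%.

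**5. Infection with antibiotics.** No arm effect, n = 212. Exposed patients are shifted by 1.0 to 1.5 SD (taxon) and 0.5 to 0.8 SD (marker). Exposure and shifts are all assumptions.
- 2% exposed: about 5%.
- 5% exposed: 6–10%.
- 10% exposed: 9–23%.

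With larger shifts (2 SD and 1 SD) the rates are 7%, 16% and 40%. Within a single arm (n = 53) and 5% exposed, shifts from 1/0.5 SD to 2/1 SD give 5–8%. Adjusting for arm does not remove this source: at 5% exposed with the 1.5/0.8 SD shifts, the rate was 9.4% without arm and 9.3% with it. It needs its own remedy.

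**The case against.** A reader might infer from the dietary rule that the samples are guarded against yogurt and probiotics but left open to antibiotics. The documents do not support that. Item 9 of the exclusions bars drugs that can cause gastrointestinal reactions, both before recruitment and during the study, and many antibiotics could fall under it. Item 3 removes some infections before entry, and concomitant drugs are recorded. A list of prohibited drugs and sample-handling rules may also stand in the full protocol, so their absence from an article is no defect. All of this stands, and it is why antibiotics are the smaller part of the point. The cover is only partial. The drug class in item 9 is undefined, and item 3 looks back four weeks from the first visit and does not reach the washout, run-in or follow-up.

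A reader might also infer that the comparison of microbiota between arms is biased. It is not: exposure unrelated to treatment is balanced on average. Some precision may be lost, but the documents give no basis for a figure.

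The correlations are neither primary nor confirmatory, and section 2.5 attaches no causal claim to them. Table 1 measures serum inflammation markers only at M0 and M3, so that route is closed at M12. These points limit the consequence. They do not answer the covariate set, which section 2.5 states outright.

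Finally, an arm-induced correlation is what one would see if the microbiota mediated the effect. But it is equally what one would see if it did not, so the pooled correlation cannot tell the two apart.

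**Conclusion.** The point holds for the participant-level correlations in section 2.5. With sex and age as the only covariates and arms pooled, about 8% to 41% of tests would be significant without any within-arm link, against a nominal 5%. This rests on the protocol's own 0.55 SD marker shift, on assumed taxon shifts of 0.3 to 1.0 SD in the berberine arms, and on 212 evaluable patients. If the correlations are run within arms, this part disappears.

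The antibiotic part is secondary: negligible at about 2% exposed, 6–10% at 5% exposed, and dependent throughout on inputs that the documents do not give. Nothing here touches the HbA1c primary outcome. It is a small improvement to an exploratory analysis.

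**What to change.** - In section 2.5, add treatment arm to the covariates of the partial Spearman correlations.
- Use the existing record of combined medications (section 2.4.3) to flag stool and plasma omics samples taken within a fixed window after systemic antibiotics, with the window set before unblinding. Repeat the correlations without flagged samples as a pre-specified sensitivity analysis.
- Keep the randomised comparison of microbiota on the intention-to-treat set. Removing flagged samples there would condition on an event after randomisation.

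The cost is a change of wording and one derived variable, with no new procedure. There are two small downsides: a few samples drop out of a sensitivity analysis, and the arm-adjusted correlation describes association within arms only, which the report should say.
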